#### Breastfeeding

Women will be asked whether they had the intention to breastfeed and whether they are breastfeeding at T0 and T1 by using ‘yes’ and ‘no’ questions.

### Demographics

Questions on the socio-demographic background will be included consisting of questions on country of birth, educational level, partner status, previous or current psychologic/psychiatric treatment, previous and or current medical treatment, medication use, fertility treatment, planned pregnancy, care in pregnancy, complications during pregnancy, following a pregnancy course and preference for mode of delivery (vaginal birth or caesarean section) prior to the actual mode of delivery. Furthermore, medical data on the delivery itself and demographics will be extracted from the electronic patient file or the birth report as made by the community midwife.

### Sample size calculation

Based on a mean difference between two treatment arms of at least 10 points on the PCL-5 scale and a standard deviation of 20, 86 patients are needed for this study to be included in each arm. Considering up to 20% loss to follow-up, 108 patients need to be included per treatment arm. We consider this sample size calculation to be conservative; the mean and difference estimates used were based on previous studies with PCL-5 score as the primary endpoint [61, 62]. The calculation was performed in PASS v11 [63] using an alpha of 0.05 and a power of 90.3%.

### Data management

Privacy of participants will be guaranteed by assigning a different number to each participant starting with 1 for the first patient who is included in the study. All gathered data from the participants will be stored under this number. The data being gathered consists of paper questionnaires and digital data. The key between the participant’s code and the data will be stored by the researchers in an online file which is secured with a password in a secured digital database. The data from the questionnaires are gathered using a secured, encrypted connection (https) and are stored in an online, password-protected, secured database that is only accessible by the researchers via Castor EDC. Data will be exported into separate SPSS to be used for statistical analyses.

Interview data on paper will be stored in a locked closet, in a locked room under the participant number, and only the researchers have access to the key. At the end of the study, data will be inserted in the same SPSS file as the electronic data for analyses.

Data will be kept for 20 years in accordance with national guidelines. We will submit modifications to this protocol to the approving ethical committee, the institutional review board, participants and investigators.

Due to the minimal risks of the early intervention EMDR and the short time span of the intervention, a data monitoring committee is deemed unnecessary.

### Statistical analysis

#### Primary study parameters

For the CAPS-5, an independent *t*-test will be performed to compare symptom severity scores between groups at T1. If the assumption of normality is violated, a Mann-Whitney *U* test will be performed. A linear mixed model analysis will determine the difference between the intervention group and the CAU group in changes in PTSD symptom severity as measured by the PCL-5 measured at inclusion and at follow-up (T0 and T1). Changes in scores of the PCL-5 will be modelled as a function of the intervention group (EMDR therapy, standard), time of measurement (T0–screening, T1 follow-up), and the interaction between time and intervention. Previous and current psychological treatment, educational level, parity, mode of delivery (vaginal birth, caesarean section, vacuum-assisted birth) and place of birth (at home, in the hospital under medical care, in the hospital under care or the midwife) will be entered as covariates. Per protocol analyses and intention-to-treat analyses will test the main effect of treatment condition, the main effect of time and the interaction effect. The assumptions of normality, homogeneity of variances and sphericity will be tested prior to interpreting the results. Furthermore, adverse events will be reported, and chi-square tests will be done to test differences in the prevalence of adverse events between the intervention and the control group.

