## Methods and design

### Aim

The main purpose of the study is to determine the safety and effectiveness of ‘early intervention EMDR’ in preventing PTSD or reducing symptoms of PTSD at 9 weeks postpartum in women with a traumatic birth experience, and to compare these results with care as usual (CAU) in women who experienced their delivery as a traumatic event. Safety is defined as the absence of all of the following adverse events: increased suicidal ideation, serious self-injurious behaviour or crisis contacts for any of the aforementioned reasons [37]. It is hypothesized that early intervention EMDR therapy is safe and that women who receive early intervention EMDR will report significantly less PTSD (symptoms) 9 weeks after the delivery compared to women who receive no treatment. Furthermore, our secondary objectives are to determine the effects of early intervention EMDR therapy on FoC, QoL, mother-infant bonding (MIB), breastfeeding and depression. It is hypothesized that early intervention EMDR will significantly reduce FoC, improve QoL and MIB, increase the success of breastfeeding and prevent or reduce depressive symptoms as compared to CAU.

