#### The CAU group

The CAU group will receive care as provided currently which means no treatment for their traumatic birth experience. However, participants in this group will receive two telephone calls between 14 and 35 days postpartum to monitor the course of symptoms regarding their traumatic birth experience. These conversations will be conducted by the researcher. Preferably, no professional psychological treatment will be given during the study period as to not bias the results. Therefore, when a participant is stable but wishes to receive EMDR treatment, she will be asked to wait for therapy until she has filled in the last questionnaires and the Clinician-Administered PTSD Scale of DSM-5 (CAPS-5) interview is conducted at the end of the study period (T1). When symptoms of PTSD significantly worsen during the study period, women will be referred to their general practitioner who can then refer the patient to a psychologist or psychiatrist when needed. When professional psychological help regarding the birth trauma is started within the study period, this will be registered and reported as a deviation of the protocol.

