### Interrater reliability and treatment fidelity

Patients, therapists and researchers will not be blinded due to the nature of the study. Assessment of the CAPS-5 interview will be conducted by an independent trained clinical interviewer, who is not aware of the randomization result. The therapists are independent of the research team and work at different sites outside the hospital. Patients in the EMDR therapy group will be randomly and equally distributed among therapists. All EMDR sessions will be recorded on video and randomly rated for treatment fidelity. During the entire study, duration group supervision every 2 to 3 months is obligatory for all therapists. After each first session with a new patient, a case conceptualization will be sent for supervision including the story of the traumatic event, with a hierarchy of the most relevant traumatic moments (targets) regarding the current impairment. Deviations from the protocol will be noted and reported. If known, therapists register when a patient terminates the study and the reason for stopping. Furthermore, they inform the PI about it as soon as possible. Women who withdraw from treatment will be invited to fill in the previously mentioned questionnaires and the CAPS interview.

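### The only blinded outcome, CAPS-5, is compared by an unadjusted T1 test that, as written, omits women without an interview and leaves the T0 and T1 PCL-5 unused

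*Protocol article*

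**What the plan says.** Under Primary study parameters the protocol fixes the CAPS-5 method: "For the CAPS-5, an independent *t*-test will be performed to compare symptom severity scores between groups at T1". The fallback is also an observed-value test: "If the assumption of normality is violated, a Mann-Whitney *U* test will be performed". Neither has a covariate or a baseline term.

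Under Effectiveness, CAPS-5 is taken at T1 only, by an assessor unaware of allocation. The PCL-5 is collected in both arms at T0 and again at T1, and is analysed by a linear mixed model with covariates. The intention-to-treat sentence in the same section names treatment, time and interaction effects, which only the mixed model has.

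The planning values under Sample size calculation are on the PCL-5: "Based on a mean difference between two treatment arms of at least 10 points on the PCL-5 scale and a standard deviation of 20". They lead to a requirement of 86 women per arm, which the section then raises to allow for attrition: "Considering up to 20% loss to follow-up, 108 patients need to be included per treatment arm".

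On follow-up, Interrater reliability and treatment fidelity says: "Women who withdraw from treatment will be invited to fill in the previously mentioned questionnaires and the CAPS interview". Under The CAU group, "when a participant is stable but wishes to receive EMDR treatment, she will be asked to wait for therapy until she has filled in the"; the rest of that sentence names the final questionnaires and the CAPS-5 interview at T1.

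**The concern.** The hypothesis in Aim is that "women who receive early intervention EMDR will report significantly less PTSD (symptoms) 9 weeks after the delivery compared to women who receive no treatment". That is a statement about the women randomised. A T1 test on interviewed women answers it without bias only if the women not interviewed leave the arm difference unchanged.

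The protocol treats its two primary PTSD measures unevenly. The PCL-5 mixed model can keep a woman who has T0 data only, and it adjusts for covariates. The CAPS-5 test does neither, so the two analyses can rest on different sets of women. The weaker method falls on the one outcome with a blinded assessor; the other outcomes are self-reported by women who know their allocation.

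Two features make differential loss plausible. Women learn their allocation after T0, and the comparison arm receives no treatment. The stated follow-up invitation covers women who withdraw from treatment, and only the EMDR arm has a study treatment to withdraw from. If symptomatic CAU women miss the interview more often than symptomatic EMDR women, a real benefit is diluted; the reverse inflates it. The direction is not known in advance.

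**Working it through.** **1. The plan's own figures.** Inputs from Sample size calculation: difference 10, SD 20, 86 per arm, alpha 0.05 (two-sided reproduces the result). Noncentrality = 10 / (20 × √(2/86)) = 3.28, and the noncentral t gives power 90.3%, as stated. Inflation: 86 / 0.8 = 107.5, so 108 per arm. At the full planned loss, 216 − 172 = 44 women have no CAPS-5.

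**2. Bias of the observed-case difference.** Let m be the share missing in an arm and g the mean of missing minus the mean of observed women. The full-arm mean is the observed mean + m × g, so

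observed difference (CAU − EMDR) = true difference − (m_CAU × g_CAU − m_EMDR × g_EMDR).

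With m = 0.20 in both arms the shift is 0.20 × (g_CAU − g_EMDR):

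- g equal in both arms: 0
- g differs by 5 points (0.25 SD): 0.20 × 5 = 1.0 point, 10% of a 10-point effect
- g differs by 10 points (0.5 SD): 2.0 points, 20%

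Symptom-related loss is therefore not enough to cause bias. It has to differ between arms.

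**3. Simulation.** The following are assumptions, not in the document: T0 PCL-5, T1 PCL-5 and CAPS-5 jointly normal; SD 20 and true difference 10 carried over from the PCL-5; 20% loss in each arm; correlation 0.5 between T0 PCL-5 and each T1 measure, and 0.75 between T1 PCL-5 and CAPS-5. Odds ratios are per SD. The imputation column assumes every woman who misses the interview returns the T1 PCL-5.

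| Missed interview depends on | Arm affected | Odds ratio | t-test | Adjusted for T0 PCL-5 only | Imputed from T0 and T1 PCL-5 |
|---|---|---|---|---|---|
| T1 PCL-5 | CAU | 1.5 | 8.8 | 9.2 | 10.0 |
| T1 PCL-5 | CAU | 2 | 8.1 | 8.7 | 10.0 |
| T1 PCL-5 | EMDR | 2 | 11.9 | 11.3 | 10.0 |
| CAPS-5 itself | CAU | 2 | 7.4 | 8.0 | 8.9 |
| Either, equal loss | both | 2 | 10.0 | 10.0 | 10.0 |

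The one-arm shifts run from (10 − 8.8)/10 = 12% to (10 − 7.4)/10 = 26%. If both arms follow one common curve, the less symptomatic arm loses slightly fewer women. Loss is then no longer equal, and the shift is 2% to 10% for odds ratios 1.5 to 2.5.

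**4. Dependence on T1 PCL-5.** In the second row, imputation gives 10.0 if all women who miss the interview return the T1 PCL-5, about 9.3 to 9.4 if half do, and 8.7 if none do. The last figure is the same as adjusting for T0 alone.

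**5. Loss tied to T0 PCL-5 only.** With loss related to T0 in one arm (log-odds slope 0.7 per SD, correlation of T0 PCL-5 with CAPS-5 0.4 to 0.6), the t-test shifts by 10% to 16%. Adjusting for T0 PCL-5 brings it to within about 1%.

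**6. Power at 86 per arm, SD 20.** 90.3% at 10, 75% at 8.1 and 67% at 7.4.

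**The case against.** Imputation rules and sensitivity analyses are usually left to a full protocol or SAP, which is not shown, and a t-test can be run on imputed data. Both statements are correct. It would be too strong to say that the test can only ever use interviewed women, or to fault the article for lacking a missing-data section. The point rests on the method the article does fix: an unadjusted T1 comparison that makes no use of the PCL-5.

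A reader might infer that the document itself predicts symptom-related loss that differs by arm. It does not. CAU women who want EMDR are asked to wait until after the CAPS-5 interview, which is arguably a reason to attend. Women who worsen are referred and any treatment started is recorded as a deviation; nothing says they leave the study. Avoidance being a PTSD symptom does not show that the arms differ.

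A reader might also take 20% as the expected CAPS-5 loss, or quote a general bias of 10% to 30%. The 20% is a planning ceiling from the PCL-5 calculation, and the document gives no CAPS-5 SD or effect. The percentages depend on assumed correlations and a one-arm mechanism; the table's largest shift is 26%.

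It is fair that the protocol already offers some protection: the PCL-5 mixed model, the invitation to treatment withdrawers, and a comparison of completers with non-completers. The last is descriptive and corrects nothing in the CAPS-5 estimate. Nor does the protocol call the t-test its intention-to-treat analysis; that wording fits the mixed model.

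**Conclusion.** The concern stands as a conditional one. The stated CAPS-5 comparison uses interviewed women only and sets aside PCL-5 data already collected in both arms. It is biased only if loss differs between arms in rate or in its relation to symptoms, which is plausible but not established. Under the assumptions listed, symptom-related loss in one arm shifts the estimate by about 12% to 26%, in either direction; the same mechanism with equal loss gives about 0%. The sample size itself is not in question. Because the direction cannot be known beforehand and the repair is cheap, the method should be changed before the data are analysed.

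**What to change.** In Primary study parameters, make the main CAPS-5 comparison one that includes all randomised women, by either of two routes:

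- multiple imputation of T1 CAPS-5, separately by arm, from T0 PCL-5, T1 PCL-5 where present and the listed covariates, analysed with adjustment for T0 PCL-5; or
- one joint mixed model of T0 PCL-5, T1 PCL-5 and T1 CAPS-5, reporting the arm difference in CAPS-5 at T1.

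Keep the observed-case t-test as a sensitivity analysis. Add a delta analysis that shifts the missing values in each arm separately, scaled to the observed CAPS-5 SD because the plan gives none. In Interrater reliability and treatment fidelity, extend the T1 invitation to women who leave in either arm.

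The cost is wording and some analysis time, with no new patients, visits or measurements. The result then relies on a missing-at-random model given PCL-5. Correction is only partial where T1 PCL-5 is missing too (about 8.7 instead of 8.1 against a true 10) or where loss depends on CAPS-5 itself (about 8.9 instead of 7.4). The delta analysis is there to show how much that residual matters.

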**Methods:**

The PERCEIVE study is a randomized controlled trial. Women suffering from the consequences of a traumatic birth experience will be randomly allocated at maximum 14 days postpartum to either EMDR therapy or ‘care-as-usual’. Patients in the EMDR group receive two sessions of therapy between 14 (T0) and 35 days postpartum. All participants will be assessed at T0 and at 9 weeks postpartum (T1). At T1, all participants will undergo a CAPS-5 interview about the presence and severity of PTSD symptoms. The primary outcome measure is the severity of PTSD symptoms, whereas the secondary outcomes pertain to fear of childbirth, mother-infant bonding, breastfeeding, depression and quality of life. The study will be conducted at a large city hospital and at multiple midwifery practices in Amsterdam, the Netherlands.

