### Procedures and interventions

When women agree to participate, they will receive a home visit from the researchers to ensure women acknowledged the information and to fill out an informed consent. After screening and providing informed consent, participants will be randomly allocated to either the EMDR therapy or the CAU group within 14 days postpartum (see Fig. 1). Randomization will be on a 1:1 basis by block randomization with random block sized of two, four or six, performed using Castor EDC [38]. After completing the baseline assessments (T0), participants will be informed in which group they have been randomized.

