#### Effectiveness

Other outcome variables will be assessed using multiple questionnaires. After randomization, but prior to the treatment (T0), both groups will receive the PTSD checklist for DSM-5 (PCL-5) [44], World Health Organization Quality of Life Questionnaire-BREF (WHOQOL-BREF) [45], Postpartum Bonding Questionnaire (PBQ) [46], Wijma Delivery Expectancy/Experience Questionnaire version B (W-DEQ B) [47], Early Postpartum Depression Scale (EPDS) [48] and questions on breastfeeding (see Figs. 1 and 2). While the experiences of the women are leading in this study, the results of patients’ questionnaire scores will not influence the inclusion and randomization process. Questionnaires will be sent through Castor with a unique ID code. If participants do not have access to a computer, the questionnaires will be provided on paper with a return envelope.

Nine weeks postpartum (at T1), each participant in both groups will undergo a CAPS-5 interview [49] and will receive the same questionnaires as at T0. To establish whether the time criterion (i.e. criterion F) of the DSM-5 criteria for PTSD has been met, the CAPS-5 interview will be conducted 4 weeks after the last EMDR therapy session in the intervention group, which corresponds to 9 weeks postpartum. The CAPS interview will be conducted by an independent person who is blinded to the randomization and who has received official training in assessment of the CAPS as to not bias the results. The CAPS version regarding symptoms in the last month will be used.

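### The CAPS-5 comparison is an unadjusted T1 test that uses no T0 data, while the CAU rules give an arm-specific reason for selective missingness that could bias it either way

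*Protocol article*

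**What the plan says.** The abstract states that "The primary outcome measure is the severity of PTSD symptoms". Under Primary study parameters, two instruments carry that outcome and are analysed differently.

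- **CAPS-5.** An independent t-test, with Mann-Whitney as fallback, "will be performed to compare symptom severity scores between groups at T1". No baseline term or covariate is attached to it. The Effectiveness section places the interview at T1 only, where "each participant in both groups will undergo a CAPS-5 interview" by a blinded assessor.
- **PCL-5.** A linear mixed model with T0 and T1 scores, arm, time, their interaction, and a list of covariates (psychological treatment, education, parity, mode and place of birth).

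The same section names intention-to-treat and per-protocol analyses, but for the effects of treatment, time and their interaction. A test at a single time point has no time or interaction effect.

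On loss, the Sample size calculation says: "Considering up to 20% loss to follow-up, 108 patients need to be included per treatment arm". On controls, The CAU group section says that a woman who is stable but wants EMDR is to be deferred: "she will be asked to wait for therapy until she has filled in the last questionnaires and the Clinician-Administered PTSD Scale". Nothing comparable is described for the EMDR arm.

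**The concern.** The CAPS-5 is the only outcome scored by a blinded assessor, and its comparison stands among the primary analyses. With a single measurement, a t-test run as written drops every woman without an interview. That is unbiased only if missingness is unrelated to severity within each arm, or if its effects cancel between arms.

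The deferral rule makes this doubtful. A control with persisting symptoms who wants EMDR has a reason to complete T1 that a recovered control lacks, and that women already treated lack too. Equally, a symptomatic control who does not want to wait has a reason to leave. Either way, the interviewed controls may not represent all controls. The test as written uses none of the information collected at T0 that could correct part of this.

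**Working it through.** **The plan's own figure.** The inputs, given where the sample size is derived, are "Based on a mean difference between two treatment arms of at least 10 points on the PCL-5 scale and a standard deviation of 20"; the error rate and power are stated as "using an alpha of 0.05 and a power of 90.3" per cent. The standardised effect is 10/20 = 0.5 SD. With 86 per arm, a two-sided t-test has noncentrality 0.5 × √(86/2) = 3.28 on 170 degrees of freedom, and power is 90.3%. Inflation: 86/0.8 = 107.5, rounded up to 108. Both figures reproduce. They refer to the PCL-5; no difference or SD is given for the CAPS-5, so the results below are in SD units.

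**Assumptions for the check (not in the document).** 108 per arm; 20% missing in each arm; random loss in the EMDR arm; severity normal with SD 1.

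**Step 1: two-level completion in controls.** Suppose that completion is 90% on one side of median severity and 70% on the other (80% overall). The half-normal mean is 0.798, so the observed control mean shifts by

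(0.45 − 0.35) × 0.798 / 0.8 = 0.10 SD.

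At 95%/65%: (0.475 − 0.325) × 0.798 / 0.8 = 0.15 SD.

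If completion follows a variable correlated 0.75 with CAPS-5 (for example T1 PCL-5), multiply by 0.75: about 0.075 and 0.11 SD.

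With about 86 observed per arm, SE = √(2/86) = 0.1525. With no true effect, the two-sided error for shifts of 0.10 and 0.15 SD is about 10% and 17% instead of 5%. A simulation of 1,500 trials per setting agrees: 0.07 to 0.10 SD with 6–10% error at 90/70, and 0.11 to 0.15 SD with 12–17% error at 95/65.

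**Step 2: logistic selection in controls, both directions.** Missingness depends on severity with an assumed odds ratio (OR) per SD. The bias is the mean severity of the observed controls.

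| OR per SD | Bias (SD) | Milder controls missing: chance of false result favouring EMDR (nominal 2.5%) | Sicker controls missing: power at 0.5 SD |
|---|---|---|---|
| 1.5 | 0.08 | 7.5% | 80% |
| 2 | 0.13 | 13.6% | 70% |
| 3 | 0.19 | 24.2% | 57% |

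The size is the same in both directions; only the sign changes. The bound, with the mildest 20% of controls all missing, is φ(−0.84)/0.8 = 0.28/0.8 = 0.35 SD.

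**Step 3: when there is no bias.** With random 80% completion in both arms, the simulated bias is 0.00 and the error 4.5%. With identical selection and rate in both arms and no true effect, the shifts cancel.

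**Step 4: what planned data can recover.** Assume correlations of 0.5 (T0 PCL-5 with CAPS-5 and with T1 PCL-5) and 0.75 (T1 PCL-5 with CAPS-5).

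- *T0 PCL-5 only.* If completion follows CAPS-5, a 0.10 SD shift carries a T0 shift of 0.05, and adjustment removes 0.5 × 0.05 = 0.025, a quarter. If it follows T1 PCL-5, it removes 0.025 of 0.075, a third.
- *T0 and T1 PCL-5, completion following CAPS-5.* R² = (0.25 + 0.5625 − 2 × 0.5 × 0.75 × 0.5)/(1 − 0.25) = 0.58, so about 58% is removed if T1 PCL-5 is known for all women. In the simulation a joint model removed about 40–60%, with T1 PCL-5 available for 50% or 100% of women without an interview.
- *T0 and T1 PCL-5, completion following T1 PCL-5.* The simulated bias falls to 0.00–0.02 SD (90/70) or 0.00–0.04 SD (95/65).

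**The case against.** The strongest reply is that the article never restricts the CAPS-5 comparison to interviewed women. A t-test can be run on imputed data, intention-to-treat is named, and handling of missing data is commonly left to an analysis plan that is not shown. This stands in part: a reader might infer that a complete-case analysis is planned and that the result cannot be an intention-to-treat estimate, but the text says neither. What remains is what the article does fix: an unadjusted test that uses no T0 data, next to an adjusted mixed model for the self-report scale. The planned comparison of completers with non-completers (Other study parameters) describes selection but does not correct the estimate.

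A second tempting inference is that the deferral rule makes the trial lean towards EMDR. The text does not support a sign. The rule is a request to stable controls, and those unwilling to wait may leave. Controls who start therapy early are recorded as protocol deviations, not as losses, and women who withdraw from treatment are still invited to the questionnaires and the interview (Interrater reliability and treatment fidelity). The last two provisions limit missingness without settling its direction.

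Third, a reader might suppose that many women without an interview will have a T1 PCL-5 because it can be completed remotely. Nothing in the document shows this, and the deferral covers the questionnaires as well as the interview. This limits what imputation can recover.

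Finally, the completion splits, odds ratios, correlations and one-arm selection are assumptions, and 20% is an upper allowance. That is correct, and the sizes should be read accordingly.

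**Conclusion.** The point holds in a direction-neutral form. The CAPS-5 test as fixed uses neither T0 PCL-5 nor covariates and, unless scores are imputed, only interviewed women, in a trial whose own rules could make missingness depend on severity in one arm.

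Under the assumed 20% loss per arm with selection in controls only, the bias is about 0.07 to 0.15 SD, reaching 0.19 SD at an odds ratio of 3. Against the 0.5 SD design effect, 0.07 to 0.15 SD is 14–30%, although that benchmark belongs to the PCL-5. The bias may inflate or hide an effect. It is smaller if loss is below 20%, and absent under the conditions in Step 3. The document establishes the possibility, not that the bias will occur or which arm it would favour.

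**What to change.** In Primary study parameters:

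- Make the main CAPS-5 analysis a comparison of all randomised women by arm, adjusted for T0 PCL-5 and the covariates already listed. Report the adjusted mean difference with its 95% CI.
- Handle missing CAPS-5 by multiple imputation done separately by arm, or by an equivalent joint likelihood model, using T0 PCL-5, the covariates and T1 PCL-5 where available.
- Keep the interviewed-only t-test as a sensitivity analysis.
- Add a delta analysis that shifts the imputed scores in both directions until the conclusion changes.

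If the full analysis plan already contains this, one aligning sentence is enough. No new data, visits or change in care are needed.

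The cost is modest programming and some reliance on self-report to inform blinded scores, which is why imputation is by arm and the interviewed-only result stays visible. Where T1 PCL-5 is missing too, only about a quarter to a third of the bias is removed under the assumed correlations; the delta analysis has to cover the rest.

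### Two instruments, CAPS-5 and PCL-5, share the primary analysis with no rule on which decides the trial, and power is stated for the PCL-5 only

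*Protocol article*

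**What the plan says.** The Methods part of the protocol abstract promises a single endpoint: "The primary outcome measure is the severity of PTSD symptoms". It attaches no instrument, contrast or analysis set.

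Under Statistical analysis, Primary study parameters, two analyses follow:

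- **CAPS-5.** A two-sample t-test, or a Mann-Whitney test if normality fails, "will be performed to compare symptom severity scores between groups at T1".
- **PCL-5.** A covariate-adjusted linear mixed model for the difference between arms "in changes in PTSD symptom severity as measured by the PCL-5 measured at inclusion and at follow-up (T0 and T1".

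On analysis sets, the same section says: "Per protocol analyses and intention-to-treat analyses will test the main effect of treatment condition, the main effect of time and the interaction effect". Neither set is ranked above the other.

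The Sample size calculation rests on one instrument: "Based on a mean difference between two treatment arms of at least 10 points on the PCL-5 scale and a standard deviation of 20". This gives 86 evaluable women per arm, and 108 per arm after allowing for 20% loss, "using an alpha of 0.05 and a power of 90.3" per cent. No CAPS-5 difference or SD appears anywhere.

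The Effectiveness section and the section on interrater reliability and treatment fidelity give the CAPS-5 to an independent interviewer blinded to allocation. The latter also says that patients are not blinded. The Discussion counts the independent CAPS-5 interview among the study's strengths.

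**The concern.** The sections point in different directions. The abstract has one outcome, the sample size uses the PCL-5, the Discussion stresses the CAPS-5, and the primary analysis section lists both. A reader cannot tell what result would make the trial positive.

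The choice matters because the instruments are not equally protected against bias. Women know their allocation by the time they complete the PCL-5 at T1, whereas the CAPS-5 is rated by a blinded interviewer. If the two disagree, nothing in the protocol stops the unblinded self-report from carrying the claim. The same question arises if the mixed model gives different answers in the ITT and per-protocol sets.

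Two quantities are at stake: the type I error of the trial's main claim, and whether the stated power applies to the test that makes it.

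**Working it through.** **1. The stated power.** Inputs from Sample size calculation: difference 10, SD 20, 86 per arm, alpha 0.05 (sidedness not stated; two-sided fits the figure).

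- Standardised difference: 10/20 = 0.5.
- Noncentrality: 0.5 × √(86/2) = 3.279, with 170 degrees of freedom.
- Power of the two-sided two-sample t-test: 0.9032. This matches 90.3%.
- Loss to follow-up: 86/0.8 = 107.5, so 108 per arm and 216 in total. This also matches.

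The arithmetic is right. It describes an unadjusted two-sample comparison of the PCL-5 at full alpha.

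**2. Does it carry over to the planned PCL-5 contrast?** With two time points, complete data and no covariates, the group-by-time interaction is a two-sample test of change scores. If 20 is the SD of a single score and r is the T0–T1 correlation, the SD of change is 20 × √(2(1 − r)). The protocol gives no r, so these values are assumptions:

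| r | SD of change | Power, 86 per arm |
|---|---|---|
| 0.3 | 23.66 | 78.7% |
| 0.4 | 21.91 | 84.5% |
| 0.5 | 20.00 | 90.3% |
| 0.6 | 17.89 | 95.4% |
| 0.7 | 15.49 | 98.8% |

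If 20 is already the SD of change, power is 90.3% whatever r is.

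**3. CAPS-5 power.** It cannot be derived, because no CAPS-5 difference or SD is given. It equals 90.3% only if the standardised difference is also 0.5. As an illustration with assumed values, a 4-point CAPS-5 difference at 86 per arm has power 90.3% with SD 8, 74.2% with SD 10 and 58.5% with SD 12.

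**4. False-positive rate if any one significant result counts.** The protocol does not state this rule; it is the assumption being examined. The rates come from simulation with no true effect, 86 per arm and 20,000 trials per setting. Assumed inputs are a CAPS-5/PCL-5 correlation of 0.5–0.9, r of 0.3–0.7, and a per-protocol set of 70–90% of the EMDR arm.

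| Tests counted | Chance of at least one p < 0.05 |
|---|---|
| CAPS-5 at T1 and PCL-5 interaction, one set | 8.8–9.8% |
| The same two in ITT and per-protocol | 10.8–13.3% |

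For scale, two independent tests give 1 − 0.95² = 9.75%. The rate stays close to that even when the instruments correlate strongly. The CAPS-5 is compared at T1 and the PCL-5 as a change, which weakens the correlation between the two test statistics.

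If both instruments had to be significant, the rate would not exceed 5%.

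**5. Cost of keeping both with either sufficient.** Splitting alpha gives 0.025 per instrument. At a standardised difference of 0.5 and 86 per arm, power is 84.4%. Restoring 90.3% takes about 102 evaluable women per arm: 102/0.8 = 127.5, so 128 enrolled per arm instead of 108.

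**The case against.** **The article condenses a fuller document, and multiplicity rules and analysis-set definitions usually sit in the analysis plan.** This is fair for the definition of the per-protocol set and for detailed testing rules. It does not cover the main point. The article is not silent: it announces one primary outcome, analyses two under the primary heading, and sizes the trial on one of them. Which endpoint decides is a protocol matter.

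Four stronger readings are tempting, and the documents do not support them:

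- **That the trial's actual error rate is some 9–15%.** Any such figure needs a rule that one significant result is enough, which no section states, and correlations that the documents do not give. The upper part of that range also counts the model's main effect of treatment as a route to success, although the section frames the PCL-5 question as a difference in change, which is the interaction.
- **That the 90.3% power belongs to no planned analysis.** It refers to the PCL-5, one of the two listed instruments, and step 2 shows that it equals the power of the planned change contrast under ordinary conditions.
- **That both instruments are tested in both analysis sets.** The sentence on sets names treatment, time and interaction effects, which are mixed-model terms. Extending it to the CAPS-5 t-test is inference, so the 11–13% figure is conditional on that as well.
- **That per-protocol analysis removes the worst controls.** The CAU section says only that professional help for the birth trauma, if it "is started within the study period, this will be registered and reported as a deviation of the protocol". It does not say that these women are excluded. If the worst-scoring controls were removed, the EMDR advantage would shrink, so this would not help a claim of success.

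**Conclusion.** The concern holds in a limited form. The protocol does not say whether the blinded CAPS-5 or the self-reported PCL-5 decides the trial, and it leaves the ITT and per-protocol runs of the mixed model unranked. That rests on the text alone.

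The sizes are conditional. The 90.3% is correct for an unadjusted PCL-5 comparison. For the planned PCL-5 change contrast it ranges from 78.7% to 98.8% as the assumed T0–T1 correlation runs from 0.3 to 0.7, unless 20 is the SD of change. For the CAPS-5 no power is established. The false-positive rate is about 9–10% only if either instrument alone may carry the claim, and about 11–13% only if both instruments are also counted in both sets.

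It should be settled before results are seen, because afterwards the choice of lead test can follow the data.

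**What to change.** In Statistical analysis, Primary study parameters:

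- Name CAPS-5 total severity at T1, in all randomised women by allocated arm (ITT), as the only primary analysis at two-sided 0.05.
- Make the PCL-5 comparison the first key secondary analysis, tested confirmatorily only if the CAPS-5 result is significant.
- Label per-protocol analyses as sensitivity analyses.

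In the abstract, attach the CAPS-5 at T1 to the primary outcome.

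In Sample size calculation, say that 90.3% is for an unadjusted PCL-5 comparison, and whether 20 is the SD of a single score or of change. Add that 86 per arm gives 90.3% for the CAPS-5 only if its standardised difference is also 0.5. Mark that as an assumption and give the CAPS-5 SD behind it.

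The cost is wording, with no extra participants if the 0.5 assumption is accepted. The price is that a significant PCL-5 result alone no longer counts as primary success. If the CAPS-5 standardised difference is expected to be below 0.5, the trial has less than 90.3% power for its lead test, and that should be stated.
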